#### **4.4 Exclusion Criteria**

- 4.4.1 Patients, or healthy volunteers, unable or unwilling to sign the Informed Consent.
- 4.4.2 Thalidomiders with very gross abnormalities and unlikely to complete the neurological and investigation assessments. Healthy volunteers unwilling to comply with the study protocol.
- 4.4.3 Patients who do not have unequivocal thalidomide –induced anomalies and nervous system symptoms.
- 4.4.4 Individuals with hereditary congenital limb reduction and related abnormalities.
- 4.4.5 Women of child-bearing potential who are pregnant.

#### **4.5 Study Programme**

- 4.5.1 The pilot study will consist of two out-patient sessions on the same day. During the first session thalidomiders will have a clinical history taken and a clinical examination. In the second session, a clinical neurophysiological evaluation will be carried out: this will last 2-3 hours.
- 4.5.2 Healthy subjects will be evaluated during a single session where they will undergo neurophysiological assessments.

#### **4.6 Methodology**

##### **4.6.1 Sensory Examination**

Dermatomal light touch and pin- prick on a 2 point scale as follows: normal=2, impaired=1, absent=0.

Referred pain will be assessed on a Visual Analogue Scale: 0=no pain, 10=worst pain.

##### **4.6.2 Motor Examination**

Muscle strength of upper limb (elbow flexors, wrist extensors, elbow extensors, finger flexors, finger abductors) and lower limb (hip flexors, knee extensors, ankle dorsiflexors, long toe extensors, ankle plantar flexors) will be assessed and key muscles will be scored on a 5 point grading scale as shown below:

- 5 = active movement, full range of motion, against gravity and provides full resistance
- 4 = active movement, full range of motion, against gravity and provides some resistance
- 3 = active movement, full range of motion, against gravity
- 2 = active movement, full range of motion, gravity eliminated
- 1 = palpable or visible contraction

0 = total paralysis

Thalidomiders will have limitations (variable degree) with performing this test due to their musculo-skeletal variants; these limitations will be recorded in the Clinical Report Form and will be taken into account when analysing data.

#### 4.6.3 ***Reflexes***

Biceps, triceps, knee, and ankle reflexes as follows: 2=normal, 1=diminished, 0=absent.

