seen. In the cervical spine, especially, spondylosis of the intervertebral joints is common spondylolysis / spondylolisthesis may occur at L5. Spina bifida occulta and, less frequently, spinal canal stenosis also occur in thalidomiders.

c) *Bony pelvis* – shows varying degrees of aplasia with sacrum being malformed or partly absent, absent pubic ramus, deficient or absent hip socket.

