## **2. PURPOSE OF THE STUDY**

The purpose of the study, therefore, is to define more precisely the contribution of peripheral nerve damage, irrespective of the cause, experienced by the Thalidomiders.

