## **3. AIM OF STUDY**

To characterise, using established clinical and investigational tools, any peripheral neuropathy (sensory, motor and sympathetic) in a cohort of middle-aged Thalidomiders.

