### **4.3 Inclusion Criteria**

4.3.1 Patients identified from the Register will be invited to participate in the clinical study.

Healthy volunteers, aged between 18 to 65 inclusive and with no neurological or musculo-skeletal disorders, will also be invited to participate.

4.3.2 Patients and healthy volunteers will have read and understood the Patient and Healthy Volunteer Information Sheets, respectively, and signed the appropriate Informed Consent forms.

4.3.3 All thalidomiders enrolled will have upper limb anomalies and clinical features suggestive of peripheral and / or central nervous system abnormalities.

4.3.4 All invitees will be able to undergo the neurological examination, nerve conduction studies, sympathetic skin responses and thermal threshold testing, albeit limitations may be imposed by anatomical abnormalities.

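### The reflex scale in 4.6.3 stops at normal although 4.3.3 admits patients with central features alone, so the reflex score cannot help separate central from peripheral causes (minor, cheap to improve)

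*Protocol*

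**What the plan says.** **Reflexes.** Protocol section 4.6.3 gives the whole scale in one line: "Biceps, triceps, knee, and ankle reflexes as follows: 2=normal, 1=diminished, 0=absent". The top grade is normal.

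**Who enters.** Section 4.3.3 reads: "All thalidomiders enrolled will have upper limb anomalies and clinical features suggestive of peripheral and / or central nervous system abnormalities". The matching exclusion in 4.4.3 removes "Patients who do not have unequivocal thalidomide –induced anomalies and nervous system symptoms"; it does not say that the symptoms must be peripheral.

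**What the study is for.** Section 3 sets out to characterise "any peripheral neuropathy (sensory, motor and sympathetic) in a cohort of middle-aged Thalidomiders". Section 2 gives the purpose as "to define more precisely the contribution of peripheral nerve damage, irrespective of the cause, experienced by the Thalidomiders". Both are confined to the peripheral nervous system.

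**What is expected in this population.** Section 1.3.2(b) describes spondylosis in the cervical spine as common and adds: "Spina bifida occulta and, less frequently, spinal canal stenosis also occur in thalidomiders". Section 1.2.2 says that central nervous system defects may also occur.

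**What else is measured.** Light touch and pin-prick (4.6.1), muscle strength (4.6.2), nerve conduction with the soleus H reflex (4.6.4), sympathetic skin response (4.6.5), thermal thresholds (4.6.6) and needle EMG (4.6.7). Section 4.5.1 also provides for a clinical history and examination of the patients, and section 5.1.1 places clinical data in the clinical notes.

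**The concern.** The protocol admits patients whose features may be central, describes spinal disease that could affect the cord, and then grades reflexes on a scale with no room for the reflex sign that would point to a central cause. A brisk reflex is put together with a normal one, or not scored.

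This matters because several of the other measures do not localise a lesion. Reduced light touch or pin-prick, weakness, raised thermal thresholds and an absent sympathetic skin response can each follow from damage anywhere along the pathway, central or peripheral. If the reflex score cannot flag the patients in whom a central cause is plausible, abnormalities on these measures are more easily read as peripheral neuropathy, which is the condition that the study exists to characterise.

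**Working it through.** The protocol states no figure on this point, so there is nothing to reproduce. The check is whether the sections fit together.

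1. **Can the scale record a reflex above normal?** No. Section 4.6.3 has three grades, 0, 1 and 2, and grade 2 is normal. An exaggerated reflex has to be scored 2 or left blank.

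2. **Can a patient with central features only be enrolled?** Yes. The and/or wording in 4.3.3 is met by central features alone. Section 4.4.3 asks only for nervous system symptoms, and no other exclusion in 4.4 removes such a patient.

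3. **Is a central or cord cause foreseeable here?** Yes, on the protocol's own account. Section 1.3.2(b) names common cervical spondylosis and some canal stenosis. Section 1.1.3 lists cervical spondylosis among the factors that make it difficult to identify a thalidomide-induced neuropathy.

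4. **Do the other measures separate central from peripheral causes?** In part:
   - Light touch and pin-prick, strength, thermal thresholds and sympathetic skin response: not by themselves, because each depends on the whole pathway.
   - Nerve conduction and needle EMG: they assess larger nerve fibres and muscle directly, so weakness or loss of touch with normal results would raise the question of a central cause. They do not test the small sensory fibres behind thermal sensation or the sympathetic fibres behind the skin response. A normal conduction study therefore leaves the origin of an abnormal thermal or sympathetic result open.
   - H reflex: soleus only, so it says nothing about the arms, where every enrolled patient has anomalies. Section 4.6.4 also adapts conduction studies to the patient's anatomy.

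5. **Is a central abnormality classed as peripheral neuropathy anywhere?** No. The protocol has no classification rule. Section 5.1.1 says only that data will be analysed statistically, and a case definition may sit in an analysis plan that is not at hand.

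6. **Could a later analysis plan repair the gap?** Not reliably. It can define neuropathy, but it cannot split a score of 2 into normal and brisk once both have been recorded alike. Patients are examined on one day (4.5.1).

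**Size.** One patient is 1/20 = 5% of the patient cohort. The number of enrolled patients who would have brisk reflexes is not given and could be zero, so no shift in any result can be computed.

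**The case against.** The strongest reply is that the reflex score does not stand alone. Patients have a full history and examination, and an examiner is free to write brisk reflexes or other cord signs in the notes. Nerve conduction and EMG look directly at nerve and muscle. The central involvement described in section 1.2.2 concerns mainly the special senses and cranial nerves, which would not be expected to change limb reflexes. Section 1.3.2 reports spondylosis and stenosis but not cord damage. The Lay Summary describes a cohort chosen for pain, numbness and pins and needles, which makes a large central-only group less likely.

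Most of this stands, and it is why the point is minor. It does not remove the gap. Free text in the notes is optional, whereas 4.6.3 is the only prescribed reflex measure. Conduction and EMG leave the small-fibre and sympathetic results unguarded, and the sympathetic component is named in the aim.

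A reader might go further and infer that cord disease cannot be found in the data at all, or that its weakness and sensory loss will be counted as peripheral neuropathy. The protocol supports neither. The notes, conduction studies and EMG can reveal some of it, and no section says how an abnormal test is to be classified.

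A reader might also want to put a figure on the bias by assuming that a few of the 20 patients are misclassified. That would rest on an invented count, on every such patient being free of peripheral neuropathy yet labelled positive, and on an outcome proportion that the protocol does not name.

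**Conclusion.** The point holds in a limited form. The reflex scale cannot register a reflex above normal, although patients with central features alone are eligible and spinal disease is expected in this population. The reflex score therefore cannot help separate central from peripheral causes, and abnormalities on the non-localising measures risk being attributed to peripheral neuropathy. Nerve conduction and EMG reduce that risk for larger fibres but not for thermal or sympathetic findings.

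This rests on reading the and/or in 4.3.3 as written, and on the general clinical assumption that exaggerated limb reflexes are a sign of central disease. The effect on the results cannot be quantified from the protocol. It is a gap in data capture, minor in weight, and worth closing because it costs almost nothing and cannot be reliably closed afterwards.

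**What to change.** - **Section 4.6.3:** add one grade above normal, for example 3 = increased (brisk, with or without clonus).
- **Reporting:** present patients with any increased reflex separately. Where their nerve conduction is normal, describe the origin of a thermal or sympathetic abnormality as indeterminate.

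Two neighbouring changes are not needed. Section 4.3.3 need not be narrowed to require a peripheral feature: that would select more strongly on the condition being measured, at a stage (register and questionnaire) before the examination that could localise the lesion. Nor should abnormal conduction be required before a thermal or sympathetic finding is called peripheral: that would discard isolated small-fibre or sympathetic neuropathy, which falls within the aim.

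**Cost:** one extra scale level on reflexes that are already being tested, and a small subgroup reported on its own. No added visit, equipment or patients.

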#### 4.6.4 ***Nerve Conduction Studies***

Nerve conduction studies (NCS) will be carried out using a Medtronic EMG machine using surface recording and stimulating electrodes and will include the following:

(a) Upper limb - median (sensory and motor), ulnar (sensory and motor), superficial radial (sensory).

(b) Lower limb - peroneal (motor), tibial (motor), sural (sensory), soleus H Reflex.

The NCS will take into account the patient's anatomy (normal, deranged), in the upper and/or lower limbs.

#### 4.6.5 ***Sympathetic Skin Response***

The sympathetic skin response (SSR) will be carried out with a Medtronic EMG machine using surface electrodes. The recording electrodes will be applied to palmar and/or plantar sites taking into account the patient's anatomy (normal, deranged). The SSR will be evoked by a single pulse electrical stimulus.

#### 4.6.6 ***Thermal Threshold Testing***

Thermal threshold to cool sensation, warm sensation, cold pain and heat pain will be measured with a SENSELab-THERMOTEST Modular Sensory Analyser; a thermode (25 x 50 mm) will be applied to the skin to be tested in the distal part of the upper and / or lower limbs. Thermal sensory thresholds will be measured using the method of limits: subjects will receive successive, decreasing or increasing, thermal stimuli from a starting temperature and will be required to arrest the changing stimulus intensity by pressing a button as soon as they perceive the specific modality being tested.

#### 4.6.7 ***Electromyography (EMG) Examination***

Needle electromyography will be carried out using a Medtronic EMG machine and a standard needle recording electrode. At least one upper limb and/or lower limb proximal and distal muscles will be examined to look for possible neuropathic or myopathic changes.

## **4.7 ADVERSE EVENTS**

### **4.7.1 DEFINITIONS**

**Adverse Event (AE):** any untoward medical occurrence in a patient or clinical study subject.

**Serious Adverse Event (SAE):** any untoward and unexpected medical occurrence or effect that:

- **Results in death**
- **Is life-threatening** – *refers to an event in which the subject was at risk of death at the time of the event; it does not refer to an event which hypothetically might have caused death if it were more severe*
- **Requires hospitalisation, or prolongation of existing inpatients' hospitalisation**
- **Results in persistent or significant disability or incapacity**
- **Is a congenital anomaly or birth defect**

Medical judgement should be exercised in deciding whether an AE is serious in other situations. Important AEs that are not immediately life-threatening or do not result in death or hospitalisation but may jeopardise the subject or may require intervention to prevent one of the other outcomes listed in the definition above, should also be considered serious.

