### **4.7.2 REPORTING PROCEDURES**

All adverse events should be reported. Depending on the nature of the event the reporting procedures below should be followed. Any questions concerning adverse event reporting should be directed to the Chief Investigator in the first instance.

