#### **4.7.3 Non serious AEs**

All such events, whether expected or not, should be recorded.

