#### **4.7.4 Serious AEs**

An SAE form should be completed and faxed to the Chief Investigator within 24 hours.

All SAEs should be reported to the <name of REC> where in the opinion of the Chief Investigator, the event was:

- 'related', ie resulted from the administration of any of the research procedures; and
- 'unexpected', ie an event that is not listed in the protocol as an expected occurrence

Reports of related and unexpected SAEs should be submitted within 15 days of the Chief Investigator becoming aware of the event, using the NRES SAE form for non-IMP studies. Local investigators should report any SAEs as required by their Local Research Ethics Committee, Sponsor and/or Research & Development Office.

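### Section 4.7.1 makes unexpectedness part of the SAE definition, while 4.7.4 uses it only to select SAEs for the ethics committee; a serious event regarded as expected would lose the SAE form and 24-hour limit

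*Protocol*

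**What the plan says.** Section 4.7.1 of the protocol defines an adverse event with no expectedness condition: "any untoward medical occurrence in a patient or clinical study subject". It defines an SAE as "any untoward and unexpected medical occurrence or effect that" leads to one of five listed outcomes: death, threat to life, hospitalisation, lasting disability or congenital anomaly. It then allows medical judgement for other situations: "Important AEs that are not immediately life-threatening or do not result in death or hospitalisation but may jeopardise the subject" may also count as serious.

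Sections 4.7.2 to 4.7.4 set the reporting routes:

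- 4.7.2, general rule: "All adverse events should be reported. Depending on the nature of the event the reporting procedures below should be followed".
- 4.7.3, non-serious events: "All such events, whether expected or not, should be recorded".
- 4.7.4, SAEs: "An SAE form should be completed and faxed to the Chief Investigator within 24 hours".
- 4.7.4, ethics committee: "All SAEs should be reported to the <name of REC> where in the opinion of the Chief Investigator", the event was both related and unexpected. Here the second term has a definition: "unexpected', ie an event that is not listed in the protocol as an expected occurrence". These reports are due within 15 days of the Chief Investigator becoming aware of the event.

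**The concern.** Seriousness describes the outcome of an event. Expectedness describes whether the event was foreseen. A reporting scheme normally uses the first to decide what is sent in quickly and the second to decide what is passed on to the committee. Section 4.7.4 is built that way, but 4.7.1 puts expectedness into the entry condition.

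Two things follow from the wording. First, the expectedness test in 4.7.4 selects nothing if every SAE is already unexpected by definition. Second, a serious event that someone regards as expected has no clear route. At stake are the classification of such an event, its form and its deadline, and so the completeness of the SAE count. Sample size, power and the analysis of the neurophysiological measurements are not affected.

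**Working it through.** No arithmetic applies. The check takes an event with a listed serious outcome, for example a hospitalisation, that is regarded as expected, and follows it through each section.

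| Section | Condition in the text | Result for this event |
|---|---|---|
| 4.7.1, adverse event | untoward | met: it is an adverse event |
| 4.7.1, SAE | untoward, unexpected and a listed outcome | not met: it is not an SAE |
| 4.7.1, medical judgement | important events outside the listed outcomes | does not apply: hospitalisation is a listed outcome |
| 4.7.2 | any adverse event | applies: must be reported, but no form or time limit is given here |
| 4.7.3 | non-serious events | does not fit: the outcome is serious |
| 4.7.4, form within 24 hours | SAE | not triggered |
| 4.7.4, committee within 15 days | SAE, related and unexpected | not triggered |

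The event therefore falls between 4.7.3 and 4.7.4 and is held only by the general sentence in 4.7.2.

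How often this could happen depends on what *unexpected* means in 4.7.1, which neither defines it nor refers to 4.7.4. There are three cases:

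1. **The 4.7.4 definition is carried back to 4.7.1.** An event is unexpected if the protocol does not list it as expected. The visible text lists 0 such occurrences, so every event is unexpected. Every event with a listed outcome is then an SAE, and nothing is lost. The expectedness test in 4.7.4 passes everything, and the committee report depends on relatedness alone.
2. **The word in 4.7.1 is read by ordinary judgement.** A serious event thought to be expected, for instance from a participant's existing condition, drops out as the table shows.
3. **A list of expected occurrences is added later and 4.7.1 is left as it is.** Any listed event with a serious outcome would then leave the SAE definition, even on the 4.7.4 meaning.

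With expectedness removed from 4.7.1, all three cases agree on entry. Every event with a listed outcome is an SAE and triggers the form within 24 hours. Those judged related and unexpected go on to the committee within 15 days, so the filter in 4.7.4 again has a purpose.

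Exposure is small: 20 thalidomiders plus 10 healthy volunteers make 30 participants. Sections 4.5.1 and 4.5.2 give the patients two out-patient sessions on one day and the volunteers a single session.

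**The case against.** The strongest reply is that the protocol has only one definition of *unexpected*, in 4.7.4, and that with no list of expected occurrences it makes every event unexpected. On that reading no serious event is excluded, and what remains is a redundant test rather than two instructions that cannot both be followed. This stands as a limit on the practical effect. It does not remove the point, because 4.7.1 does not adopt that definition and the agreement would end once a list was added. The count of 0 also holds only for the text available, since the appendices named in the contents are not shown.

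A reader might infer more than the text supports, in four ways:

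- **That an expected serious event is handled as non-serious and merely recorded.** Section 4.7.3 covers non-serious events only, and a hospitalisation does not become non-serious by being expected. Section 4.7.2 still requires it to be reported.
- **That the expectedness decision passes from the Chief Investigator to whoever first sees the event.** Section 4.7.1 assigns the decision to nobody, 4.7.2 directs reporting questions to the Chief Investigator, and 4.7.4 reserves the related-and-unexpected opinion to that role. A shift is possible in practice, but it is not stated.
- **That serious harm from electrical stimulation, needle electromyography or thermal testing would be missed.** Nothing in the protocol suggests that death, hospitalisation or lasting disability is expected from these tests. Such an event would be unexpected on any ordinary reading and would be captured.
- **That the unfilled committee name in 4.7.4 and the absence of a list add weight.** The first is clerical, since section 6.1 names the committee. The second makes the gap narrower, not wider.

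The medical-judgement clause in 4.7.1 carries no expectedness condition, which suggests that the authors did not mean to exclude expected serious events. It does not close the gap, because it addresses only events outside the listed outcomes.

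**Conclusion.** The point holds as an inconsistency in a safety-reporting rule. Section 4.7.1 makes expectedness a condition of being an SAE; 4.7.4 treats it as a later judgement that serves only the committee report. On a literal reading, a serious event regarded as expected remains reportable under 4.7.2 but loses the SAE form and the 24-hour limit.

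The likely size is small. The gap opens only if the undefined word in 4.7.1 is read by ordinary judgement, or if a list of expected occurrences is added without changing the definition. Few events are to be expected among 30 participants tested on one day. The documents show no event actually omitted, and they do not support saying that such events would go unreported altogether. The point is worth correcting because the rule is stated wrongly and the correction costs almost nothing.

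**What to change.** In 4.7.1, delete the words *and unexpected* from the SAE definition, so that an untoward occurrence with a listed outcome is an SAE and triggers the form within 24 hours. Leave expectedness in 4.7.4 alone, as the Chief Investigator's test for the committee report. The cost is two words and, with so few participants, negligible extra reporting.

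Two editorial changes can be made at the same time: enter in 4.7.4 the committee named in 6.1, and list the expected minor effects of the test procedures so that the 4.7.4 definition has something to refer to. The list should not be added before 4.7.1 is corrected, because it would then narrow the SAE definition.
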